## Abstract

**Background:**

Construction workers are at elevated risk of suicide. MATES in Construction (MATES) is one of the few suicide prevention programs that explicitly address this problem. The MATES program includes an integrated system of services that supports prevention, early intervention and recovery (i.e., primary, secondary and tertiary prevention) for mental health problems among construction workers. In this protocol, we describe a proposed evaluation of *MATESmobile*, an electronic platform which will be accessed by workers who have undergone MATES training.

**Methods/design:**

In this protocol, we describe a Randomised Controlled Trial (RCT) which seeks to assess whether *MATESmobile* results in improved literacy regarding suicide prevention, and improved help-seeking and help-offering attitudes among those who have attended MATES training. Secondary outcomes include changes in suicide ideation, suicide attempt and psychological distress. Workers will be recruited prior to MATES face-to-face training. In total, 295 workers will be randomly assigned to the intervention condition (*MATESmobile* + face-to-face training) and 295 will be randomly allocated to the control (face-to-face training). The intervention will run for 8 weeks. Assessments will be run immediately post intervention, and at 3, 6, and 12 months

**Discussion:**

*MATESmobile* offers the potential to reinforce and enhance the effects of face-to-face training, resulting in greater skills and knowledge in suicide prevention, as well as a reduction in suicidality and distress.

**Trial registration:**

This trial is registered with the Australian New Zealand Clinical Trials Registry (ACTRN12619000625178; 26 April 2019).

## Background

Elevated rates of suicide among construction workers have been identified in many countries [1], including Australia [2]. Such elevated rates among construction workers may reflect a range of factors connected to employment in a highly-male dominated workforce, including excessive alcohol consumption, relationship problems, and lack of help-seeking [3, 4]. Aside from this, workers in construction also face a number of adverse psychosocial working conditions [5], including low job control and high psychological demands (the combination of which produces job strain) [6], low social support [7], and work-family conflict (when role pressures from the work and family domains are mutually incompatible) [8]. There are constant shifts in the landscape and organisation of construction work, as tasks, colleagues and supervisors change from project to project and job to job, contributing to feelings of job insecurity [9]. Adding to this instability is the fact that many workers are forced to meet short deadlines and experience periods of unemployment between projects [9]. The lowest skilled groups may be at most risk, especially during times of economic recession [10].

Mates in Construction (MATES) is a charity established in 2008 by the Building Employees Redundancy Trust to prevent suicide in the construction industry. MATES is an industry-based, multimodal workplace-focused charity, delivered at construction sites or company offices. Significant commitment from building site management to the program has been crucial — both to communicate organisational investment in addressing the issue of suicide, and also allow training to be completed during work hours. MATES is a multi-component prevention and early intervention program, consistent with the Australian National Suicide Prevention Strategy (‘Living Is For Everyone’ or ‘LIFE’) [11]. MATES operates over four states and, to date, training has been delivered to over 135,000 workers. The core component of the MATES training is the General Awareness Training (GAT), a 45-min face-to-face awareness session provided to all construction workers on site. GAT promotes awareness of and risk factors for suicidality. It aims to reduce stigma and encourage help-seeking and help-offering behaviour, and presents suicide as preventable. “Help offering” refers to workers offering active support to co-workers who display any suicide warning signs. Workers completing GAT are provided with a white sticker to wear on their hard hat identifying them as ‘GAT-trained’. For a site to be designated ‘compliant’, all workers on that worksite must receive GAT, with an 80% training level maintained despite staff turnover. GAT is also a component of a training program specifically for apprentices. Other components of MATES that support GAT include:“Connector training” for volunteer “gatekeepers”: Connectors help an at-risk worker access help via a trained worker, MATES Field Officer, Case Manager or other local community supports.Suicide First Aid: in which Applied Suicide Intervention Skills Training (ASIST) trained workers provide suicide first aid interventions for at-risk workers identified by Connectors.Field Officers: Field Officers are employed directly by MATES. Their job is to increase awareness, recruit new construction sites, and provide ongoing support to MATES sites through fortnightly site visits, establishing and maintaining relationships with workers on-site, and debriefing Connectors.Case managers: Suitably qualified case managers are employed to assist troubled workers with a plan to effectively address their issue(s). This could include connecting workers with such services as their EAP, financial counselling, drug and alcohol services, grief counselling, or family and relationship counselling.

Thus, MATES provides an integrated health service model aimed at prevention, early intervention, and recovery (i.e., primary, secondary and tertiary prevention).

Since its inception, MATES has been committed to evaluation and continual program improvement. A recent evaluation [12] compared age-standardised suicide rates among the construction industry to other employed males. There was evidence of a decline in suicide rates among construction workers employed in the state of Queensland (where there has been a high uptake of MATES) compared to other employed males. In 2011, another evaluation [3] assessed process related outcomes, for example, how prepared participants felt to deal with someone who was suicidal, and attitudes towards suicide. Compared to 355 workers at two sites who had not completed GAT, those who received the training showed greater improvements in knowledge about suicide.

Several other uncontrolled evaluations have also suggested that MATES is an acceptable and appropriate intervention for workers in the construction industry [13–16]. The main limitations of these evaluations are that they only assessed knowledge immediately before and after training, and therefore could not provide information on whether MATES resulted in greater retention of knowledge in the long term. Thus, this finding may reflect transient “training effects” – where an individual retains knowledge immediately post training but loses it over time. Another problem is that these evaluations were conducted in one state only, and the findings may therefore not be generalisable to other states. Lastly, these evaluations did not assess the extent to which training reduced suicide attempts and thoughts of suicide among construction workers. Thus, several questions remain about the extent to which those who take part in the program experience individual changes in relevant outcomes proximal to suicide death, such as suicide ideation, self-harm or suicide attempt, and psychological distress. Further, and most specific to this project, questions remain about the longer-term impacts of the program, and whether it would achieve better outcomes if strengthened and reinforced by additional elements.

To fill the gaps in knowledge noted above, MATES has recently developed *MATESmobile*, an electronic platform which was designed to follow MATES face-to-face GAT training. *MATESmobile* seeks to enhance and sustain the effectiveness of MATES through a smartphone approach, which we will evaluate in relation to a wider range of outcomes than assessed previously. *MATESmobile* will focus on two main elements: 1) reinforcing face-to-face training messages over time, and; 2) enabling links to mental health support should people need it. The use of a smartphone approach to deliver this program is feasible and appropriate considering the high uptake of smart phones the construction industry, where they are considered a ‘tool of trade’.

In this paper, we describe the randomised controlled trial to test the efficacy of *MATESmobile.* The evaluation seeks to evaluate the potential gains of complementing MATES face-to-face training with *MATESmobile*. *MATESmobile* will be implemented by MATES, with support from the research team named in this project. This trial is registered with the Australian New Zealand Clinical Trials Registry (ACTRN12619000625178; 26 April 2019).

## Methods

### Design

This is a two-arm individual participant randomised controlled design, following SPIRIT guidelines [17, 18].

The day-to-day management and administration of *MATESmobile* (including recruitment, roll out of intervention, and dissemination and collection of survey information) will be the responsibility of MATES.

### Program logic

The program logic of *MATESmobile* can be seen in Fig. 1. *MATESmobile* will have ongoing contact with individual participants, approximately once per fortnight over an 8-week period.

**Fig. 1 Fig1:**
[figure not shown]
Program logic for MATESmobile

This ongoing contact will reinforce messages from MATES, aiming to increase knowledge and skills in suicide prevention literacy, as well as more helpful attitudes about the extent to which suicide is preventable. The reinforcement of messages will also flow through to impact help offering (e.g., the message “MATES help other MATES”) and also help-seeking from either formal (e.g., doctors, mental health professionals, case management) or informal sources (e.g., peer support from co-workers, friends and family). At the same time, the *MATESmobile* platform will provide informational resources for those in need or at risk of suicide, including how to access to case management and other health services. It also seeks to encourage social support and community around the MATES program, leading to improvements in psychosocial safety at work. Collectively, all these aspects of the program are hypothesized to lead to improvements in primary and secondary outcomes.

### Field testing

The content of *MATESMobile* was designed by the founding organisation of the MATES program, including the National and State Chief Executive Officers and field staff. Staff employed at MATES were consulted to design program materials that were relevant and appropriately framed for the industry. This included input into the frequency and timing of content delivery, as well as the attractiveness, clarity, and usefulness of the content.

### Study setting

The study will be set in construction sites across Australia. These sites will include those managed by the Industry Partners involved in the study (who are Australia’s leading construction companies), and/or sites where MATES is operational.

### Eligibility criteria

Participants need to be recruited from a site where MATES is operational. Workers attending GAT will be considered eligible for the study.

### Study objectives and outcomes

The primary objective of the evaluation is to assess whether *MATESmobile*: a) improves suicide prevention literacy, as measured by the GAT suicide awareness questionnaire [3]; and b) improves help-seeking and help-offering attitudes, as measured by the General Help-Seeking Behaviour Questionnaire [19], and the GAT help-seeking and help-offering items. Secondary aims are to assess whether *MATESmobile* results in greater reduction in suicide ideation as measured by the 4-item Suicidal Behavior Questionnaire-Revised (SBQ-R) [20] as well as psychological distress, as measured through the Kessler-6 [21]. Changes in suicide attempt will be measured as an exploratory outcome (anticipating a potential low incidence of this outcome).

### Interventions

#### Training of field officers

There will be a standardised recruitment procedure across different construction sites. The research team will ensure that MATES field staff are well informed about both the program, and how to explain it to potential participants. The MATES Project Manager will train field officers about how to introduce and recruit participants to the study.

#### Intervention condition

After completion of standard GAT face-to-face training, those allocated to the *MATESmobile* program will be contacted via smartphone application every two weeks for 8 weeks with information about how to access the program and reminders. We will conduct baseline assessment (a longer survey) prior to the 8 week intervention, followed by smaller assessments at 3, 6 and 12 months.

#### Control condition

Those in the control arm will complete a baseline survey, GAT training, and additional surveys at 3, 6 and 12 months following baseline.

### Recruitment of participants

Information about *MATESmobile* will be communicated at the start of GAT by MATES field officers, prior to the delivery of the GAT content. Field officers will provide information on the project including plain language statements and the procedure for providing consent. Those who are interested in the project will be asked to complete a written baseline survey, a written consent form and provide their mobile phone number. These will be placed in a sealed cardboard box during GAT, and will be returned to the project manager at MATES. The field officers will assure participants that this identifying information will not be provided to employers or released to any other party, and that results from the study will only be available in aggregate form, with no identifying information revealed. No participants have been recruited to the trial at this time.

### Ethics and provision of care

All enrolled participants will be required to provide written consent to being involved in *MATESmobile.* If any person is identified as being at risk of suicide at the time of GAT or at a later time (identified through the survey items, e.g., the SBQ-R [20]), they will be offered connection to MATES case management and other suicide prevention help-lines, irrespective of which condition they are allocated to.

### Sample size and power calculations

Previous work on examining suicide prevention literacy in construction workers using MATES [22] found a mean difference of 0.429 on a scale of one to five in beliefs about suicide warning signs at post-intervention. Based on this, a minimum of 295 participants per group will be required to detect this difference at the nominal 0.05 significance level with 90% power. A previous study has shown that 13% of the working population report suicide ideation [23]. We believe it is realistic to expect a change from 13 to 8% prevalence following the trial. Power calculations indicate we will need 267 persons per group to detect this difference at the nominal 0.05 significance level with 90% power. Assuming 30% drop-out, we therefore aimed to recruit a total of 844 participants over a three-month period.

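### The 267 per group stated to give 90% power for suicide ideation falling from 13% to 8% does not follow from those inputs; a standard two-group comparison needs about 788 per group

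*Protocol article*

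**What the plan says.** The section on sample size and power (Protocol article, Methods) contains two calculations.

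- **Literacy.** For a mean difference in beliefs about warning signs, "a minimum of 295 participants per group will be required to detect this difference" at 0.05 with 90% power.
- **Suicide ideation.** The starting figure is "A previous study has shown that 13% of the working population report suicide ideation". The target is "We believe it is realistic to expect a change from 13 to 8% prevalence following the trial". The result is "Power calculations indicate we will need 267 persons per group to detect this difference at the nominal 0.05 significance level with 90% power".

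The section then closes with "Assuming 30% drop-out, we therefore aimed to recruit a total of 844 participants over a three-month period". The abstract gives equal arms: "295 workers will be randomly assigned to the intervention condition", and the same number to control. The section on objectives and outcomes lists suicide ideation, with psychological distress, as a secondary aim. The analysis section plans mixed models for continuous outcomes and a comparable approach for binary ones, including ideation prevalence.

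**The concern.** The section prints every input needed to check the ideation figure: two proportions, a significance level, a power and a size per group. These do not agree with each other. A difference of five percentage points at this prevalence ordinarily needs many hundreds per group, so 267 looks too small by a wide margin.

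At stake is how the ideation result will be read. Only two outcomes in the article have a power calculation, and this is one of them. Since 267 is below 295, a reader may take it that ideation is adequately powered by the size set for literacy. If power is in fact much lower, a non-significant ideation result set against a stated 90% could be taken for evidence that the app does not affect suicidal thinking.

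**Working it through.** **Inputs, all from the sample size section unless noted**

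- p1 = 0.13, p2 = 0.08, difference 0.05.
- Significance level 0.05. Sidedness is not stated; I take two-sided and also try one-sided.
- Power 90%.
- 1:1 allocation (abstract).
- Sizes per group: 267 (stated for ideation), 295 (literacy), 422 (844/2, everyone retained).

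**Formula** (pooled variance under the null, mean proportion p̄):

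n per group = [z₁₋α/₂ √(2p̄(1−p̄)) + z₁₋β √(p1(1−p1) + p2(1−p2))]² / (p1−p2)²

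**Step 1: try to reproduce 267 from the stated inputs.** With p̄ = 0.105:

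- 1.960 × √(2 × 0.105 × 0.895) = 1.960 × 0.4335 = 0.8497
- 1.2816 × √(0.1131 + 0.0736) = 1.2816 × 0.4321 = 0.5537
- n = (0.8497 + 0.5537)² / 0.05² = 787.9, so **788 per group**

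The stated 267 is about one third of this. Other standard versions do not close the gap:

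| Version, 13% vs 8% | n per group |
|---|---|
| Two-sided, 90% power, pooled | 788 |
| Same, continuity-corrected | 828 |
| Same, unpooled variance | 785 |
| Same, arcsine | 780 |
| Same, log odds ratio | 804 |
| One-sided, 90% power | 642 |
| Two-sided, 80% power | 589 |
| One-sided, 80% power | 464 |

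**Step 2: what 267 does match.** With p1 = 0.13, p2 = 0.05 and p̄ = 0.09, the same formula gives (0.7932 + 0.5136)² / 0.08² = 266.8, which rounds up to 267.

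**Step 3: power for 13% vs 8%, one timepoint, unadjusted.**

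Power = Φ{[0.05√n − 1.960 × 0.4335] / 0.4321}

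| n per group | Two-sided | One-sided |
|---|---|---|
| 267 | 47% | 60% |
| 295 | 51% | 63% |
| 422 | 66% | 77% |

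For 295: 0.05 × √295 = 0.8588; (0.8588 − 0.8497) / 0.4321 = 0.021; Φ(0.021) = 0.508.

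**Step 4: what 295 per group can detect.** Solving the same expression for p2 with p1 = 0.13, two-sided power reaches 90% when prevalence falls to about 5.3%, and 80% at about 6.2%.

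**Step 5: does the trial size depend on 267?** 2 × 295 = 590, and 590/0.7 = 843, in line with the stated 844. It does not.

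**The case against.** The strongest reply is that the trial measures people repeatedly and plans a mixed model, so a single-timepoint test is not the planned analysis. The usual variance factor for k follow-ups with baseline adjustment and a common correlation r is (1 + (k−1)r)/k − r². With the abstract's four follow-ups and an assumed r = 0.6 it equals 0.70 − 0.36 = 0.34. Applied to the unpooled 785 (784.7 before rounding), this gives 266.8, again 267, for the stated 13% versus 8%. With 295 per group and the three follow-ups given in the descriptions of the two conditions (3, 6 and 12 months), the same approximation puts power at about 85% for r = 0.3, 87% for r = 0.5 and 95% for r = 0.7.

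Part of this stands. It shows that 51% is the power of one unadjusted cross-section and not necessarily that of the planned model. It also shows that the match with 13% versus 5% is not unique, so a reader who infers that 5% was entered by mistake goes beyond the document.

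It does not rescue the statement. The protocol gives no correlation and no baseline adjustment for this calculation, and does not say the target is an effect averaged over visits. The approximation treats a binary outcome as linear, assumes the same effect at every visit and ignores the clustering by training time and location that the analysis section anticipates. A single-visit target or any clustering would lower these figures.

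It is also fair to say that the article does not rank ideation above the other secondary outcomes and does not itself claim that 295 covers it. That is a reader's inference from the two numbers.

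**Conclusion.** The statement is wrong as written. On the printed inputs, 90% power for 13% versus 8% needs about 788 per group two-sided, or 642 one-sided; 267 is about a third of the two-sided requirement. No standard two-group version tried comes near 267, so the unstated sidedness does not matter.

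The power figures (47% at 267, 51% at 295, 66% at 422) rest on these assumptions: a two-sided 0.05 test, one timepoint, no adjustment, independent participants, and 295 as the number analysed per group, which is how the drop-out inflation treats it.

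Two stronger readings are tempting and are not supported. One is that the whole trial is undersized: the 844 comes from the literacy calculation and does not move. The other is that the planned mixed model has only about 50% power for ideation: that depends on a correlation, a target timepoint and clustering that the article does not give.

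**What to change.** In the sample size section, delete the statement that 267 per group gives 90% power, and do one of the following.

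1. State that, with 295 analysed per group, two-sided power for 13% versus 8% is about 51% at a single timepoint, and that 90% power is reached only if prevalence falls to about 5.3%.
2. If a repeated-measures gain was intended, name the timepoints, the correlation and its source, any baseline adjustment, and whether the effect is averaged over visits; then recompute.

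In either case, say that the secondary ideation outcome will be reported with its confidence interval and that a non-significant result will not be read as evidence of no effect. The ranking of outcomes need not change.

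The cost is wording, plus one calculation under the second option. No extra participants are needed and the target of 844 stands. Under the first option the stated power becomes much less favourable, which is the honest position. The recruitment section says nobody had yet been enrolled, so as of the article the correction could precede any data.

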### Data collection

Participants in both conditions will complete online surveys (following the written baseline survey), which will be delivered to their smart phone via “alerts”. The “alerts” will re-direct respondents to an online survey. The surveys will be confidential, but not anonymous, as we will need to link baseline to follow up surveys, which will be done using mobile telephone numbers. Identifying information will also enable personalised re-contacts for non-response (which may be conducted via email and/or text messaging). The app will be available on Android, iOS and Windows mobile systems.

### Allocation sequence

Allocation concealment will be achieved by generating a set of computerised random numbers which will be assigned to participants. We will randomise in blocks of 50 participants. Hence, once 50 persons have returned their consent form, they will be allocated a random number. Once a block of 50 participants is obtained, the random numbers will be sent to a statistician external to the trial for allocation (discussed below).

